### Description of the parent interventions

#### Body and Soul

This program [32] aimed at increasing fruit and vegetable consumption among African American church members living in California, Georgia, North Carolina, South Carolina, Delaware, and Virginia. The components included the formation of a church coordination committee, implementation of church-wide nutrition activities to increase fruit and vegetable intake, provision of educational materials, and motivational interviewing phone calls delivered by trained peer counselors and a policy change. A total of 15 churches were randomly assigned to the Body and Soul intervention or to a comparison group. Fruit and vegetable (F&V) intakes were measured at baseline and 6-month follow-up. Participants in the intervention group consumed significantly more F&V than in the comparison group [32].

#### Healthy Body/Healthy Spirit

This program [33] aimed at increasing physical activity and fruit and vegetable (F&V) consumption among African American church members living in the greater Atlanta area. Participants were provided with an exercise videotape and guidebook; a nutrition videotape, cookbook, and an audio cassette of gospel music. Sixteen churches were randomly assigned to three intervention conditions. Group 1 received culturally tailored self-help nutrition and physical activity intervention materials. Group 2 received the same intervention materials as group 1, plus four motivational interviewing phone calls delivered by trained peer counselors while group 3 served as the control group and received standard nutrition and physical activity materials. Physical activity and F&V consumption were measured at baseline and 1 year after. Participants in the intervention groups consumed significantly more F&V and exercised more minutes per week than those in the control churches [33].

### Description of the intervention arms

A.Body, Soul, and Spirit will be modeled after the two EBIs conducted in African American churches in the USA: the “Body and Soul” and the “Healthy Body Healthy Spirit” [32, 33]. The adapted intervention, Body, Soul, and Spirit, will involve a combination of the core components of both of the parent interventions. In creating the aggregate intervention, we will select components of each of the parent trials that were deemed “essential” [38, 39]. A component was termed “essential” if it was reported to have accounted for the positive intervention effects observed in the parent trials [40, 41]. The following components of the parent trials were considered essential and will be considered for our adaptation and use (see Table 1):

a) Individual education
i.An adapted version of a cookbook [32] with healthy eating recipes, cooking techniques, storage tips for fruits and vegetables, and health benefits of increasing fruit and vegetable intake.ii.An adapted version of an exercise manual [33] and exercise video or audio CD [33] containing gospel music with biblical quotes/themes and/or brief sound bites of priest sermons sliced between songs.

b) Group education

Each participating church will receive a single copy of an adapted version of “Forgotten Miracles” [32] an 18-min video that targets fruit and vegetable intake using both spiritual and secular motivational messages. Churches will be asked to organize public screenings of the video and to make the copy available to members on request.

c) Campaigns and promotions
i.Formation of a project coordination committee: This committee will be composed of representatives of the academic and church communities and will be responsible for the implementation of the project [32, 33].ii.Church events: There will be a project kick-off event, at least one nutrition event and an additional event involving the church priest [32]. Examples of events included in the parent trials are serving fruit and vegetables after church services, at other church programs, or during the kick-off event; sponsoring food demonstrations or taste tests; organizing tours of food markets and inviting guest speakers; or having priest sermons related to health (Table 1).

**Table 1 Tab1:** Intervention components of the parent trials and adapted interventions

	Parent Trial		Adapted Intervention		
**Intervention Component**	**Body and Soul**	**Healthy Body Healthy Spirit**	**BSS (Arm 1)**	**BSS plus (Arm 2)**	**Control (Arm 3)**
A cookbook with healthy eating recipes, cooking techniques, storage tips for fruits and vegetables (F&V), and health benefits of lowering fat/increasing F&V intake	✔	✔	✔	✔	
An exercise manual with biblical themes and scripture woven throughout		✔	✔	✔	
A workout audio CD containing local gospel music with biblical quotes and brief sound bites of pastor sermons spliced between songs		✔	✔	✔	
Public screenings of “Forgotten Miracles,” a video that targets fruit and vegetable intake using both spiritual and secular motivational messages	✔	✔	✔	✔	
Constitution of a project coordination committee	✔	✔	✔	✔	
Conduct at least one health event*	✔		✔	✔	
Motivational interviewing phone calls delivered to participants by trained volunteer peer counselors	✔	✔	✔	✔	
Churches will agree to implement at least one policy change^#^	✔		✔	✔	
Faith-based text messages				✔	
Distribution of information leaflets promoting physical activity and healthy food consumption			✔	✔	✔

*Examples of some of the events included in the parent trials were serving fruit and vegetables during the kick-off event, after church services, or at other church programs; sponsoring food demonstrations or taste tests; organizing tours of food markets for parishioners; inviting guest speakers; and having priest sermons related to health

^#^Potential policy changes include establishing guidelines for the types of foods served at church functions, changing snacks served at youth camps, or creating a food pantry

d) Supportive relationships

Motivational interviewing phone calls to selected church parishioners delivered by trained church volunteers [32, 33].

e) Policy change

Churches will agree to implement at least one policy change [32]. Potential policy changes include establishing guidelines for the types of foods served at church functions, changing snacks served at youth camps, or creating a food pantry.

B. Body Soul and Spirit Plus (Bss+) will retain all the components of BSS with the addition of faith-based text messages. We will develop the content, wording, frequency, and timing of each message guided by the theoretical models mentioned above, a review of existing literature and the feedback received from the parishioners. We will then pre-test them among a small group of parishioners before use to ensure that the messages are designed to have the desired effect. The project coordinator and/or trained church volunteers will send these messages periodically at pre-scheduled intervals.

C. Usual care/Control: Information leaflets on healthy food consumption and physical activity will be distributed to parishioners in the churches in this group after a church service. This will constitute an information-based *standard of care* approach that will be used as the control condition for this group randomized trial (See Fig. 2).

**Fig. 2 Fig2:**
[figure not shown]
Flow chart for participant enrolment, baseline data collection, follow-up, and analysis

### Phases of the study

The study will be conducted in four phases.

*Phase 1—*Pre-implementation—Community entry, recruitment, and randomization of churches; partnership and capacity building; and needs assessment and situation analysis.

*Phase 2*—Intervention adaptation and development—Adaptation and design of the core components of BSS and BSS+ for use in a Nigerian setting.

*Phase 3*—Intervention implementation and delivery

*Phase 4*—Implementation evaluation—Data collection and analysis of implementation measures, study outcomes, and success criteria; calculation of an ICC, the means and variances for each the three treatment arms, effect sizes (all to potentially inform the sample size calculation in a full RCT), and the decision to determine whether or not to progress to a definitive trial.

#### Phase 1—pre-implementation

*i*) *Community entry, church recruitment and randomization:* We will work with the leadership of the diocese to recruit the 12 eligible churches from their network of churches. To be included in the study, churches must have at least 100 active members (we define “active” as members who attend church services at least weekly). We will obtain a list of the churches in the diocese and screen them for eligibility. Then, we will randomly select 12 eligible churches from this list. Selected churches will be allocated into one of three groups: BSS, BSS+, or control. Randomization will be computer-generated, with allocation concealment by opaque sequentially numbered sealed envelopes. An independent biostatistician will generate the randomization sequence in accordance with the CONSORT guidelines [42].

*ii*) *Partnership development and Capacity building:* We will create a diocesan-project steering committee (DPSC) consisting of one representative from the diocesan leadership, one representative of the diocesan medical society, two diocesan volunteers, and members of the academic research team. The DPSC will serve as the overall planning and coordination team for the intervention. In addition, in each of the eight intervention churches, we will create a local church implementing committee (LCIC), which will consist of at least two church members who are either volunteers and/or persons nominated by the vicar and members of the academic research team. The LCIC will serve as the in-house implementation team for the intervention.

Once the committees have been constituted, we will conduct a partnership development and capacity building workshop for committee members to obtain leadership and community buy-in. Workshops will initially focus on sharing the project aims with participants to obtain their support and commitment and to engage them as partners on the project. The committees will hold regular meetings where the academic researchers will work with them to identify effective ways of implementing the intervention. Thereafter, the committee members will meet at regular intervals to discuss the development, planning, and implementation of the project. Committees will decide on operational procedures and develop a plan to keep their church parishioners involved in the intervention.

*iii*) *Needs Assessment & Baseline Situation Analysis:* Qualitative methods will be used to: (i) Identify and understand the underlying factors influencing PA and eating patterns of the parishioners. (ii) Explore their underlying cultural and spiritual values/norms and how these affect PA and HFC. (iii) Explore their attitudes towards the faith-based text messages and seek their opinions on best ways to engage parishioners using such messages. (iv) Understand how best to adapt the core components of the program in their local setting.

We will conduct nine in-depth interviews with the bishop or his representative (1), church leaders/priests/members of the church governing council (5), and members of church medical societies (3). We will conduct focus group discussions (FGDs) with the church members. Participants will be stratified into three distinct groups according to their ages, i.e., the elderly > 65 years, adults 25–64 years, youth aged 18–24 years, or persons who attend the youth section of the church. Focus groups will consist of 6–12 participants per group. All interviews and FGDs will be conducted in the preferred language and setting of the participants, audio-recorded, and a research assistant will take notes during each discussion/interview.

#### Phase 2: intervention adaptation and development—adaptation of the core components of BSS and BSS+ for use in a Nigerian setting

Adaptation involves “reviewing and changing the structure of a program or practice to more appropriately fit the needs and preferences of a particular group or community” [43]. To culturally adapt the core components of the project, we will go through the five stages of cultural adaptation proposed by Barrera et al., i.e., information gathering, preliminary design, preliminary testing, refinement, and final trial [44].

*Information gathering*: First, we will gather information to determine how well the original intervention will fit the needs and preferences of our population, and if an adaptation is in fact justified.

*Preliminary design*: We will use the information gained from the first stage to inform the preliminary modifications of the original interventions while attempting to preserve the core components. This will be done using an iterative process in a series of focus group discussions and feedback sessions with the church committee members employing the same qualitative methods described earlier. Thereafter, we will draft the preliminary version of the intervention.

*Preliminary testing, refinement, and final trial*: This study is the focus of the third and fourth stages where we aim to pilot test the preliminary version and refine it with the ultimate aim of proceeding to Barrera’s fifth stage of testing the interventions in a fully powered trial.

##### Framework for program adaptation and balancing fidelity and fit

Bernal et al. [45] proposed one of the earliest models, the ecological validity model (EVM), for cultural adaptation of evidence-based interventions. This delineates eight dimensions, which we will consider when developing the cultural adaptation of the program. They are language, persons, metaphors, content, concepts, goals, methods, and context [38]. Rodriguez et al. [46] later expatiated on this to include three phases of adaptation. In the initial phase, the research team will collaborate with the members of the DPSC to find a balance between the needs of the church members and scientific integrity. Then, we will jointly identify relevant evaluation measures in the parent trials and adapt them in a process parallel to the adaptation of the intervention. The final phase will consist of jointly integrating the observations and data gathered to design the newly packaged intervention [46–48]. This process will also follow the guide for balancing program fidelity and fit as proposed by Castro et al. [49] during the program adaptation process.

In a series of workshops, the DPSC, guided by the core components of the BSS and BSS+, the results of the needs assessments, focus groups, feedback sessions, and the models described above, will carry out the project adaptation process. They will review the study protocol and intervention materials, consider session-by-session analysis of each component and recommend possible modifications to ensure the spiritual and cultural acceptability to the parishioners. Based on the recommendations of the workshop participants, modified intervention materials will be created. The end-result will form the initial draft of the Body, Soul, and Spirit program.

##### Development of the faith-based text messages for BSS+

The diocesan project steering committee and the members of the academic team will jointly develop a series of faith-based text messages designed to promote PA and HFC for church members. We will design the messages considering the World Health Organization (WHO) recommendations for physical activity and healthy eating and using the guidelines proposed by Abroms et al. [50] for developing and pretesting text messages for behavioral change, which are as follows:

a) Conduct formative research for insights into church members’ health behaviors and opinions of faith-based text messages to promote PA and F&V intake: In a series of focus group sessions with the project committee and church members, we will explore the opinions of the church members about physical activity and fruit and vegetable consumption, the possible barriers to these health behaviors, and their opinions about receiving text messages to help them overcome these barriers.

b) Design the text messages (TM): Then, we will identify our key behavioral change goals. Our objectives for the TM component are to provide knowledge and/or fill in identified knowledge gaps, modify attitudes, address known barriers to change, and motivate people to take action towards our key study outcomes. A key consideration in designing the faith-based messages is to establish the link between biblical themes and our behavioral change goals. Guided by our communication objectives, theoretical models and using the insights garnered from the focus groups and the literature, we will develop the TM framework (i.e., frequency, timing, wording, language) and form the faith-based TM library. This will be done using an iterative process of feedback sessions with the church committee members.

c) Pretesting and revising the text messages: We will identify a small set of church members (less than 30) in similar churches that are not part of our study. We will pre-test these messages using the agreed TM framework, solicit the feedback from the participants on the wording, content, and perceived effect of the messages. Thereafter, we will make appropriate modifications till a final version of the TM library and framework is agreed upon. Then, we will adopt this for use as the **+**PLUS component of the BSS**+** intervention arm.

Finally, based on the drafts developed for the BSS and BSS+, the DPSC in another series of workshops, will develop an action plan for the programs and present this plan to the Bishop or his representative for his input prior to adoption. These will serve as the action plans for BSS and BSS+ programs.

#### Phase 3: intervention delivery/implementation

We will employ a three-arm group randomized pilot study design using 12 churches (4 in each group). The intervention will operate at two levels. The church-wide events and environmental changes will be aimed at the entire congregation, while the distribution of exercise/nutrition videos, manuals and cookbook recipes, audio CDs, and text messages will be delivered only to individuals who voluntarily enroll and consent to participate in the study. Data will be collected at baseline 3 and 6-month time points.

Each participating church will identify 2–3 volunteers to serve as peer counselors for this project. They will participate in the recruitment of study participants and undergo peer-counselling training for the program. Volunteers will have a background in a “health-related profession” (e.g., physician, nurse, or other health worker) and will be required to attend a training, make four intervention calls to at least five members of each church, and undergo a performance evaluation before engagement. This training will provide knowledge and general skills in patient recruitment, research ethics, and motivational interviewing techniques like asking open-ended questions, reflective listening, and specific strategies to elicit discussions about PA and HFC. They will be asked to recruit and make at least four intervention calls to at least five study participants. Peer counselors will receive a small stipend for their time and effort with participant recruitment and retention and calling cards to cover the cost of the phone calls. In addition, regardless of the treatment arm, churches (rather than participants) that achieve the minimum targets for participant recruitment and retention will be provided with an incentive worth $100 or less at the end of the study.

#### Phase 4

Implementation evaluation—This will involve quantitative and qualitative data collection and analysis of implementation measures (i.e., participant recruitment and retention; Program participation and satisfaction and data collection completion), the calculation of parameter estimates for subsequent sample size calculations for the future trial, evaluation of the program success criteria, and a decision to determine whether or not to progress to a definitive trial.

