### Inclusion and exclusion criteria

To be eligible, participants must be adults aged 18 years or older who have been members of the church for at least 6 months and attend church services at least weekly. Eligible respondents for BSS+ must, in addition, have a text message-compatible mobile phone and have used it for at least 6 months. Acutely ill or disabled people will be excluded.

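### Peer counselors' pre-engagement calls may give some participants a full course of an intervention component before baseline, possibly in control churches too

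*Protocol article*

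**What the plan says.** The Phase 3 section on intervention delivery places counselors everywhere: "Each participating church will identify 2–3 volunteers to serve as peer counselors for this project". Their role is described as follows: "They will participate in the recruitment of study participants and undergo peer-counselling training for the program". Before taking it up they must attend a training, "make four intervention calls to at least five members of each church, and undergo a performance evaluation before engagement". The same paragraph later adds: "They will be asked to recruit and make at least four intervention calls to at least five study participants".

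Table 1, under the description of the intervention arms, lists the calls as a component ("Motivational interviewing phone calls delivered to participants by trained volunteer peer counselors"). It ticks that component for BSS and BSS+ and leaves it blank for control. In the Healthy Body/Healthy Spirit parent trial, the motivational-interviewing group received the self-help materials "plus four motivational interviewing phone calls delivered by trained peer counselors", so four calls were the full course there.

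The inclusion criteria admit "adults aged 18 years or older who have been members of the church for at least 6 months" who attend weekly. The only people excluded are those who are acutely ill or disabled. Under the recruitment strategies, trained volunteers and/or research assistants enrol eligible people in order of arrival.

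The text messages are handled differently. For their pretest the plan says: "We will identify a small set of church members (less than 30) in similar churches that are not part of our study".

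**The concern.** The two sentences about calls name different recipients (church members, then study participants) and different stages (a condition for taking up the role, then the role itself). The first set is as long as a full course and is made in the congregations from which participants are drawn. Nothing keeps its recipients out of the sample.

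If they enrol, their baseline is measured after exposure. The food questionnaire asks about the past month, so calls made in that month fall inside the recall window. Baseline means, change from baseline, effect sizes and variances could then be distorted. The study objectives and the quantitative analysis section name effect sizes and variability among the pilot's outputs for sizing the definitive trial. In a control church the same calls would deliver a component that Table 1 withholds from that arm.

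**Working it through.** The plan gives no figure on this point to reproduce. The check has two parts: the order of events, then the possible size.

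**Order of events**

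1. The training, the four calls and the evaluation form one list, which closes with the words about engagement. Four calls in total could not reach five people one at a time, so four calls per person is the workable reading.
2. Recruiting is part of the counselors' role, and the recruitment section refers to volunteers who are already trained. If the list is completed before the role starts, the calls precede recruitment by those volunteers, and so precede the baselines of the people they recruit.
3. Recruitment by research assistants alone would leave the order open. No section dates the calls against baseline.

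**Inputs**

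- Counselors per church: 2–3 (Phase 3).
- Members called per counselor: at least 5 (Phase 3).
- Participants per church: 25 (Sample size estimation).
- Active members per church: at least 100 (Phase 1). A size of 400 is my assumption, to show the range.
- Intervention churches: 8 of 12 (Phase 1).

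**Members called per church (m)**

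- Different recipients: 2 × 5 = 10 to 3 × 5 = 15. Because five is a minimum, these are lower limits for that case.
- Counselors sharing the same five: m = 5.

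**Expected overlap, assuming the 25 are a random draw from A active members**

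Expected number per church = 25 × m / A, and the share of the sample is m / A. The chance of at least one such participant across the 8 intervention churches is 1 − [C(A − m, 25) / C(A, 25)]^8.

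| m | A | Expected per church | Share | At least one in 8 churches |
|---|---|---|---|---|
| 10 | 100 | 2.5 | 10% | over 99.9% |
| 15 | 100 | 3.75 | 15% | over 99.9% |
| 10 | 400 | 0.625 | 2.5% | 99.5% |
| 15 | 400 | 0.94 | 3.75% | over 99.9% |
| 5 | 400 | 0.31 | 1.25% | 92.5% |

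**Effect on the estimates**

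Let p be the share already called and d the shift that the calls produce in an outcome. Assume d is the same for everyone and unrelated to the person's starting level. The baseline mean then moves by p × d, and the between-person variance grows by p(1 − p)d².

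- p = 0.10: 0.10d and 0.10 × 0.90 × d² = 0.09d².
- p = 0.15: 0.15d and 0.15 × 0.85 × d² = 0.1275d².

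If the shift persists, mean change from baseline in an intervention church is understated by the same p × d. The document gives no value for d, so the distortion cannot be put in servings or minutes.

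**The case against.** The strongest reply is that there is only one set of calls. Both sentences speak of intervention calls, four of them, to at least five people. The closing words on engagement may attach only to the evaluation. The outcome measures mention an evaluation after training but no completed course of calls. Referring to members of each church is also loose drafting, since taken literally every counselor would call into every church. On this reading nobody is called before enrolment. It is possible, but it fits poorly with the change of recipients and stage. It would also leave the paragraph stating one duty in two ways that do not match, which still needs correcting.

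A second reply is that recipients and timing are operational details that an article may leave out. That would be fair if the article were silent. But it states the eligibility criteria, names the recipients as church members, and gives the matching safeguard for the text messages.

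On the control arm, counselors may be there only to recruit, because recruitment is meant to run alike in all arms. The paragraph nevertheless sets the call requirement for all volunteers without naming an arm.

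The reply on consequence stands in part. Descriptive feasibility is the main analysis, change over time is not tested for significance, and effect sizes and variances are to be used alongside literature values. That limits the harm without removing it.

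**Conclusion.** The point holds as a possibility that the text leaves open: as most naturally read, some participants may have received a full four-call course before baseline, in intervention churches and perhaps in control churches. With 2–3 counselors calling different members, the expected share is about 10–15% of participants in a church of 100 active members and about 2.5–4% in an assumed church of 400. Both figures rest on random enrolment, and they are lower if counselors share recipients.

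Three stronger readings are not supported.

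- A reader might infer that some baselines do follow a full course. The document does not say that called members enrol, and it does not date the calls.
- A reader might set 10–15 called members against 25 places and infer 40–60% exposure. That is what results if every one of those members enrols, which nothing in the document suggests. With five shared recipients it falls to 5/25 = 20%.
- A reader might infer that enrolled implementers would carry the 70% retention indicator, or that focus-group members are also pre-exposed. The first needs retention rates that the document does not give. The formative discussions deliver no intervention component, and their participants are not placed in the study churches.

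This is a cheap improvement.

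**What to change.** 1. In Phase 3, state that the pre-engagement calls go to members of diocesan churches outside the 12, as is done for the text-message pretest. The diocese has 53 − 12 = 41 others. Alternatively, add to the exclusion criteria anyone who has received such a call. If only one set of calls is meant, say so and merge the two sentences.
2. Exclude peer counselors and local church implementing committee members from the 25 participants. The outcome measures and success indicators already count their retention separately.
3. Reconcile the Phase 3 paragraph with Table 1 on whether any calls are made in control churches.

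The cost is a few sentences, plus either some coordination with non-study churches or a slightly smaller pool. If recipients are made ineligible in a church of 100 active members, 100 − 15 = 85 to 100 − 10 = 90 remain for 25 places, less the few implementers. No extra staff or participants are needed.
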